## Abstract

Parkinson’s Disease (PD) is a progressive neurodegenerative disorder marked by motor and non-motor symptoms, including cognitive decline, mood disturbances, and sensory deficits. While dopaminergic treatments remain the gold standard, they present long-term side effects and limited impact on non-motor symptoms. Transcranial Pulse Stimulation (TPS) has emerged as a promising adjunct therapy in neurological and psychiatric conditions, but its effects in PD remain underexplored. This open-label, single-arm trial protocol involves 14 PD participants and outlines a personalized 12-session treatment approach combined with a homogeneously distributed TPS intervention among patients with PD. The approach addresses the subject’s most prominent symptoms, as identified through validated clinical assessments, encompassing domains related to both motor and non-motor symptoms. Over 2.5 months, besides the intervention sessions, the 14 participants will undergo an MRI brain scan, a baseline assessment, a post-treatment assessment, and a 1-month follow-up assessment. The study aims to determine whether personalized TPS is a feasible and safe intervention and whether it improves PD symptoms across multiple functional domains. This study represents the first structured attempt to evaluate a multimodal, personalized TPS intervention in patients with PD. It addresses gaps in current treatment approaches and may support the development of future strategies for integrated, symptom-targeted neuromodulation.

## 1. Introduction

Parkinson’s disease (PD) is the second most common neurodegenerative disease, affecting at least one million individuals in the United States, with annual costs estimated at approximately USD 52 billion (about USD 160 per person living in the US) [1,2,3]. Its physiopathology primarily includes loss of dopaminergic neurons in the nigrostriatal pathway, leading to reduced striatum dopamine levels [2]. PD is a complex, age-related, and progressive disorder characterized primarily by motor dysfunctions, such as resting tremors, bradykinesia, and rigidity. However, non-motor symptoms can also be present, including cognitive impairment, affective disorders, mood disturbances, and olfactory and gustatory dysfunction. All these motor and non-motor PD features associated with PD’s physiopathology may lead to mood, anxiety, and sleep disorders, which can exacerbate deficits in memory, attention, and thinking processes [4]. As a result, the combination of motor and cognitive impairments, along with behavioral disturbances, can lead to disability and a significant impact on social and occupational functioning, patients’ and families’ quality of life (QOL), and patients’ risk of morbidity and mortality [5,6].

The clinical manifestations of PD are highly heterogeneous, with patients exhibiting diverse combinations of symptoms and varying rates of disease progression. This heterogeneity has been increasingly studied through multimodal data analyses, which have identified distinct PD subtypes such as tremor-dominant, postural instability and gait difficulty (PIGD)-dominant, and rapid eye movement sleep behavior disorder (RBD)-related forms [7,8]. These subtypes differ not only in clinical progression but also in cognitive function, non-motor symptom profiles, and treatment response, highlighting the need for individualized intervention strategies. For instance, PIGD patients are more likely to develop autonomic dysfunction and sleep disturbances, whereas the RBD subtype is associated with a higher risk of cognitive decline. Additionally, recent machine learning and imaging-based studies have revealed interindividual anatomical brain differences in PD, which may underlie the divergent trajectories of motor and cognitive symptom progression [9]. Therefore, personalized symptom assessment and targeted treatment planning may enhance therapeutic outcomes and improve the quality of life for individuals living with PD.

Current therapies include pharmacological (e.g., levodopa), non-pharmacological interventions (e.g., physical therapy and speech and language therapy [SLT]), and surgical procedures (e.g., Deep Brain Stimulation [DBS]), and mainly focus on enhancing motor symptoms [10,11,12]. Dopaminergic drugs represent the gold-standard therapy for improving motor function and reducing freezing of gait episodes in PD patients [13,14]. However, prolonged use of dopaminergic drugs increases the risk of numerous side effects, including dyskinesia and behavioral dysfunction such as impulse control disorders and mood disorders [10,11]. Furthermore, dopaminergic drugs may have a long-term negative impact on patients’ cognitive status [15].

In recent years, the number of non-invasive brain stimulation (NIBS) devices for treating PD has increased significantly. These therapies are appealing as they are low-cost techniques and have an excellent safety profile, lacking side effects like those related to pharmacological or surgical methods [16,17]. The two most common non-invasive techniques, Transcranial Magnetic Stimulation (TMS) and Transcranial Direct Current Stimulation (tDCS), have shown promise in treating PD; however, recent studies with these types of NIBSs have focused primarily on PD’s non-motor symptoms or memory, and a few of them targeted in freezing of gait [17,18,19,20,21,22,23].

### 1.1. Transcranial Pulse Stimulation (TPS) in the Context of Neurological and Psychiatric Conditions

TPS is a novel NIBS technology that applies repetitive, single high-pressure ultrashort shockwave pulses within the ultrasound frequency range to stimulate the brain. Since it uses a concomitant neuroimaging by neuro-navigation device (Figure 1), TPS enables more precise, focal, and deep brain modulation, reaching depths of up to 8 cm (about 3.15 in) into the brain, for instance, modulating subcortical areas, in a targeted manner, when compared with other NIBS [24,25].

Currently, TPS has been demonstrated to be a non-invasive and painless technique with no serious adverse effects, capable of modulating neural excitability and significantly improving many neurological conditions. The biological mechanisms hypothesis behind TPS therapy involves the modulation of vascular endothelial growth factor (VEGF) and brain-derived neurotrophic factor (BDNF), which have been associated with improved cerebral blood flow and angiogenesis, as well as effects on cell permeability, proliferation, and differentiation. These factors are believed to influence cell functions such as migration, proliferation, differentiation, and apoptosis, and may contribute to neuroplasticity and neuronal repair processes, as observed in preclinical studies [26,27]. Animal experiments have also shown that the blood–brain barrier (BBB) remains intact following TPS, supporting its safety profile [28].

Although it is a novel technology, TPS has shown many positive effects in other neurological disorders, such as mild neurocognitive disorders [29,30], Alzheimer’s disease (AD) [31,32,33,34,35,36,37,38], disorders of consciousness [39], autism spectrum disorder [40,41], attention deficit hyperactivity disorder [42,43], and depression [36,44]. In most of these studies, TPS has shown considerable potential in reducing depressive symptoms and enhancing different aspects of cognitive performance. A recent observational study reported that 10 sessions of TPS therapy were safe in PD subjects and led to improvements in clinical motor function in optimized PD patients with only mild and transient side effects (fatigue [50%], headache [30%], and dizziness [30%], which resolved within one day) [45]. Their findings showed a significant reduction in the Unified Parkinson’s Disease Rating Scale part III (UPDRS-III pre-TPS: 16.70 ± 8.85, UPDRS-III post-TPS: 12.95 ± 8.55; *p* < 0.001; Cohen’s d = 1.38), and none of the participants experienced worsening of their motor status. However, this study has some limitations, primarily related to its retrospective design, small sample size, lack of a sham control group, and the heterogeneity of the study population and protocol. A study showed positive effects on the motor functions of PD patients after even a single treatment with TPS of the motor cortex M1 in comparison to a sham group [46].

Findings from AD studies suggest that TPS might induce improvements in cognitive impairment and depression symptoms, with potential application in PD for both motor and non-motor symptoms [29,44]. Fong et al. (2023) [29] observed improved cognitive function in 19 elderly participants with mild neurocognitive disorder after six TPS open-label sessions. Results showed increasing MoCA scores: pre-TPS: (19.32 ± 4.52), post-TPS (21.16 ± 3.98), and 12-week follow-up (20.58 ± 4.29), with a one-way ANOVA effects of time of F (3, 54) = 4.99, *p* = 0.004. Moreover, Cheung et al. (2023) [44] in a pilot randomized controlled trial demonstrated a reduction in depression symptoms in the TPS group (mean difference = −6.60, *p* = 0.02) in comparison to the control group in a study with 30 subjects who underwent six sessions of TPS.

Therefore, TPS as an adjunct therapy for PD needs to be validated with further empirical support. In addition, the heterogeneity in the study populations and protocols within the PD-TPS domain poses a challenge in interpreting the results comprehensively [32,38].

### 1.2. The Present Study

This study protocol outlines for the first time a personalized treatment approach combined with a homogeneously distributed TPS intervention among patients with PD, tailored to address each individual’s most prominent symptoms as identified through validated clinical assessments, involving domains related to (i) motor symptoms, (ii) cognitive impairment, (iii) depression, (iv) sleep disorders, (v) fatigue, (vi) voice function, and (vii) loss of smell and taste. The primary hypothesis is that TPS, as an adjunct therapy, encourages plasticity-dependent changes that may improve PD’s overall symptoms. In addition to the seven core domains described here, this study also investigates the safety of TPS and its potential effects on improving the freezing of gait and overall QOL in patients with PD. This study aims to assess the safety, feasibility, and potential benefits of TPS in improving PD symptoms. We hypothesize that active TPS will be safe and feasible and might lead to significant improvements in PD symptoms, such as motor and cognitive function, depression, sleep disorders, fatigue, voice and speech function, taste and smell disorders, and QOL compared with the pre-intervention baseline measures. These preliminary findings can provide a foundation for designing future RCTs to validate the therapeutic efficacy of TPS.

## 2. Experimental Design

This is an open-label, single-arm pilot study (NCT06676995) designed to assess the safety and feasibility of TPS for improving overall PD symptoms, with a total sample size of 14 subjects to be conducted at Spaulding Rehabilitation Hospital, Cambridge, USA. This study consists of a consent and enrollment visit, a magnetic resonance imaging (MRI) brain scan, 12 sessions of TPS (3 sessions per week), and 6 assessment sessions—a baseline visit, after every 3 TPS sessions, and a 1-month follow-up visit after the last TPS session. Also, 1 assessment visit will be performed after every 3 TPS sessions. See the study scheme provided in Figure 1. Participants will primarily be recruited through extensive methods such as advertisements online and in local newspapers. The inclusion criteria are as follows: (i) age between 40 and 90 years old; (ii) diagnosis of “probable” or “possible” PD, as defined by the current clinical criteria [47] or as confirmed by a co-investigator neurologist or confirmation via medical records or a letter from a patient’s physician; (iii) disease stages 2 to 4 based on the UPDRS subdomain V (or Hoehn and Yahr scale); (iv) taking a stable regimen of anti-parkinsonian medications, defined as no changes in drug type, dosage, or administration frequency, for at least 30 days before study entry.

The exclusion criteria are as follows: (i) clinical features suggestive of other causes of parkinsonism/Parkinson’s plus syndromes; (ii) history of deep brain stimulation, brain ablation surgeries, or malignant mass brain lesions; (iii) history of schizophrenia, bipolar illness, or alcohol/drug abuse within the past six months; (iv) history of psychosis or suicidal thoughts; (v) contraindications to transcranial pulse stimulation (i.e., metal objects in the head, cortisone treatments within six weeks before the first stimulation session, CNS thrombosis); (vi) unstable metabolic and psychiatric conditions (e.g., uncontrolled diabetes, uncompensated cardiac issues, uncompensated pulmonary disease); (vii) contraindications to MRI according to MGB screening in the Martinos-Center (i.e., pacemaker, defibrillator, or wires other than sternal wires, metallic foreign body in the eye, or drug infusion devices—if the models of these devices are not compatible with MRI; (viii) pregnancy; (ix) epilepsy or disorders that significantly increase the likelihood of seizures, including: severe traumatic brain injury or congenital birth defects leading to seizures; (x) bed- or wheelchair-bound patients; (xi) non-English speakers, since speech will be assessed through the Consensus Auditory-Perceptual Evaluation of Voice (CAPE-V) questionnaire, which relies on voice deviance for natural conversational speech in English.

## 3. Materials and Equipment

### 3.1. MRI Data Acquisition

T1-weighted sequences are collected using a 3 T Siemens Skyra MRI scanner (Siemens Healthcare, Erlangen, Germany) equipped with a 20-channel head/neck coil. The sequence parameters include an in-plane resolution of 230 × 256 pixels, a maximum gradient of 40 mT/m, and a slice thickness of 1–2 mm, comprising 100 to 180 slice image, and covering the forehead to the occiput and from ear to ear.

### 3.2. TPS Protocol

Subjects will receive 12 TPS sessions, administered 3 times per week over 4 consecutive weeks, using a NEUROLITH^®^ device by STORZ MEDICAL AG, Tägerwilen, Switzerland. Each treatment session will involve the application of 10,000 pulses of focused shock waves. By default, 4000 shockwave pulses with an energy flux density of 0.25 mJ/mm^2^ will be distributed homogeneously across the brain areas (as standard intervention). A total of 2000 shockwave pulses will be applied to the foot soles. Previous reports regarding patients receiving foot sole stimulation have highlighted the benefits of including the plantar surface in treatment protocols [48,49].

Clinical experience suggests that applying Extracorporeal Shock Wave Therapy (ESWT) to the plantar surface by using approximately 1500 impulses at an energy flux density between 0.10 and 0.15 mJ/mm^2^, improves the patients’ sense of ground contact and leads to a reduction in muscular stiffness in the lower limbs These effects contribute to improved mobility, gait initiation, lower limb muscle stiffness, reducing freezing episodes and overall comfort in PD [50].

The remaining 4000 shockwave pulses with an energy flux density of 0.25 mJ/mm^2^, as an individual intervention, will be distributed to up to four different brain areas based on each subject’s most prominent symptoms (Table 1). The application will be guided by a neuronavigational system using previously acquired magnetic resonance images, allowing real-time tracking of the standard and individualized target areas for precise targeting and even distribution of pulses.

## 4. Detailed Procedure

### 4.1. Intervention

The TPS session sequence will be (1) individual, (2) standard (homogeneously across all brain areas), and (3) foot sole. As previously noted, up to four specific and personalized brain regions of interest will be targeted for individual intervention. For all patients, one of these four areas will be the entire strip of the primary motor cortex (1000 pulses), and the other 3000 pulses will be chosen according to the patient’s three most important clinical features.

During treatment, a camera system will monitor the positions of both the handpiece and the patient’s head using goggles equipped with infrared markers. This individual real-time tracking system allows for standardized focal brain stimulation across the entire study population, ensuring proper movement of the handpiece over the skull, as displayed in Figure 2. Furthermore, it will enable the tracking of the stimulation pulses, with each pulse leaving a colored mark in the visualization. The TPS intervention will use an energy flux density of 0.25 mJ/mm^2^ at a focus depth of 5 cm, with the useful energy dispersed between 2 and 8 cm. The frequency of application (pulse repetition rate) will be set at 4 Hz, with a coupling medium of water-based gel applied to the scalp.

During TPS, a generous amount of bubble-free ultrasound gel is applied sequentially to the skin and hair in the treatment area to prevent any acoustic impedance barriers. TPS application will be conducted in a continuous sweeping motion, lasting approximately 40 to 45 min per session, resulting in a total applied energy of 50 Joules (5 mJ/pulse with 0.25 mJ/mm^2^). The handpiece will be kept perpendicular to the skull for highly focused applications throughout the treatment. The entire treatment session will then be recorded for subsequent evaluation of the precise localization of individual intracerebral pulses, as presented in Figure 3.

The 12-session protocol consisting of 40 to 45 min of treatment over 4 weeks for PD, was developed, suggesting that frequent and consistent transcranial pulsed stimulation (TPS) sessions can maximize neuroplasticity and symptom management benefits. Additionally, this protocol is supported by prior studies demonstrating that repeated sessions over a short duration may optimize therapeutic outcomes by maintaining the neural changes induced by TPS, and that administering the treatment over a 3–4 week period may enhance both the efficacy and safety of TPS [31,34,36]. In contrast to other neuromodulation techniques such as tDCS and TMS, TPS has the potential to be applied less often, with more focused areas being treated.

### 4.2. Assessments and Outcomes

To assess motor and non-motor functions in PD subjects, this study protocol proposes the use of the following assessments: Unified Parkinson’s Disease Rating Scale (UPDRS) [51], Non-Motor Symptoms Scale (NMSS) [52], SCales for Outcomes in PArkinson’s disease-COGnition (SCOPA-COG) scale [53], Freezing of Gait Questionnaire (FOGQ) [54], Timed Up and Go (TUG) test [55], Parkinson’s Disease Sleep Scale (PDSS-2) [56], Parkinson’s Disease Fatigue Scale (PFS-16) [57], Beck Depression Inventory-Second Edition (BDI-II) [58], Visual Analog Mood Scale (VAMS) [59], Visual Analog Scale (VAS) for Olfactory and Gustatorial evaluation [60], Voice Handicap Index (VHI-10) [61], Consensus Auditory-Perceptual Evaluation of Voice (CAPE-V) [62], Voice acoustic characteristic [63], Parkinson’s Disease Questionnaire-39 (PDQ-39) [64], VAS for Pain; Brief Neurological Exam; Acceptability of Intervention Measure (AIM) scale and Feasibility of Intervention Measures (FIM) scale [65], and Patient’s Qualitative Assessment of Treatment—Real-World (PQAT-RW) [66]. The intervention strategy is defined after the baseline visit (visit 3), based on the pre-defined criteria displayed in Table 1 and Figure 3.

### 4.3. Safety

Adverse effects (AEs) questionnaires will be applied after every intervention session, allowing participants to grade the severity (mild, moderate, or severe) and indicate the perceived relationship to the intervention (none, remote, possible, probable, or related). In addition, a 20-min resting-state EEG will be conducted to monitor brain activity and investigate potential epileptiform discharges at baseline, after the first session, and after every three sessions (weekly), including a follow-up. Although not intended as a sole safety measure, EEG data will complement our clinical monitoring. Safety will also be assessed through clinical outcome scales (UPDRS, NMSS, and SPMSQ), where the absence of significant deterioration between baseline and post-intervention will support safety conclusions.

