### 4.4. Data and Statistical Analysis

Data forms and questionnaires will be coded in a standardized format and entered into our database. Digital measures/recordings will be similarly tracked in our database and regularly backed up. Analyses will be conducted using standard statistical software such as STATA version 18.5 and R version 4.4.2.

The primary outcome will be a change in the UPDRS total score from the baseline. Secondary outcomes include change scales that measure improvements in UPDRS subdomains, motor and cognitive function, mood symptoms, sleep disorder, fatigue, voice quality, olfactory and gustatory disorder, freezing of gait episodes, and QOL comparing pre- and post-TPS. These results will be used to determine the best effect of TPS intervention for a more extensive study in patients with PD. Differences between the two groups (pre- and post-TPS) will be tested using a paired Student’s *t*-test, and, in addition, we will also test the time effect in general mixed regression models adjusting for age, gender, and PD severity. This model will be used for the primary and secondary outcomes. Secondary analyses will be conducted as exploratory, and for this reason, we will not apply formal correction for multiple comparisons. Since this is a pilot study with a small sample size, our aim is to identify possible trends and generate hypotheses for future confirmatory trials. Accordingly, all results from secondary analyses will be interpreted with caution. A similar analysis will be conducted for the adverse effects. We will also use the uncorrected *p*-value for safety analysis to increase the likelihood of detecting harmful adverse effects.

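### Non-significant worsening on three scales in 14 patients is to support safety without any margin; one scale passes more often than not up to about 0.57 SD of true mean worsening

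*Protocol article*

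**What the plan says.** Safety is a stated aim in the Abstract and in sections 1.2 and 2. Section 4.3 describes three sources of evidence.

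- Questionnaires: "Adverse effects (AEs) questionnaires will be applied after every intervention session", graded by the participant for severity and relatedness.
- EEG at baseline, after the first session, weekly and at follow-up: "Although not intended as a sole safety measure, EEG data will complement our clinical monitoring".
- Scales, introduced with "Safety will also be assessed through clinical outcome scales (UPDRS, NMSS, and SPMSQ", where the list ends, and followed by the operative clause: "where the absence of significant deterioration between baseline and post-intervention will support safety conclusions".

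Section 4.4 supplies the test: "Differences between the two groups (pre- and post-TPS) will be tested using a paired Student’s *t*-test". A mixed model for time is added. On multiplicity it says: "We will also use the uncorrected *p*-value for safety analysis to increase the likelihood of detecting harmful adverse effects".

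Section 4.5 sets n = 14 for a two-tailed test at alpha 0.05, sized on a benefit of d = 1.5, with no allowance for dropout.

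Section 4.2 opens its inventory with "this study protocol proposes the use of the following assessments". UPDRS, NMSS, SCOPA-COG and a brief neurological exam are in it; SPMSQ is not.

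**The concern.** The clause turns failure to find harm into support for safety. That inference is sound only if the test would probably have found harm large enough to matter. The document does not say what size of worsening matters, and the trial was sized only for a very large benefit. A small trial is then favoured by its own smallness: fewer patients, or more dropouts, make a non-significant result more likely.

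The comparison is also of group means, so patients who get worse can be offset by patients who improve.

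At stake is a published statement that the scales support safety when the data could not exclude a moderate mean worsening. Section 5 already reasons this way, anticipating that the absence of severe adverse events would prove TPS safe. The caution in section 4.4 about interpretation is attached to the secondary analyses, not to this clause.

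**Working it through.** **Inputs.** n = 14, two-sided, alpha 0.05 (section 4.5); paired t-test (section 4.4); an SD of around 20% (section 4.5). No harm margin is given, so true worsening is varied as an assumption. It is written d, in units of the SD of the paired change.

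**The plan's own figure.** Paired t-test power comes from the noncentral t with n − 1 df and noncentrality d√n. At d = 1.5 and n = 14, power is 99.9%, so the claim of at least 80% is true. The smallest n giving 80% is 6 (83%), so 14 does not reproduce as a minimum. That is a separate matter, and nothing below depends on it.

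**One scale.** P(no significant deterioration) = P(T ≤ 2.160), with T noncentral t on 13 df and noncentrality d√14 = 3.742d.

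| True mean worsening (SD of change) | No significant deterioration, n = 14 |
|---|---|
| 0.2 | 90% |
| 0.3 | 82% |
| 0.4 | 72% |
| 0.5 | 59% |
| 0.57 | about 50% |
| 0.8 | 21% |
| 1.0 | 7% |
| 1.5 | 0.1% |

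An 80% chance of flagging worsening needs d = 0.81. If the test were one-sided at 5%, the 50% point would move from 0.57 to 0.46 SD.

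**Percentage points.** If the 20% SD is the SD of the change (an assumption; section 4.5 does not say), 0.57 SD is about 11 points. A 10-point worsening (0.5 SD) then goes unflagged 59% of the time and a 15-point worsening 26%.

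**Three scales together.** Simulated normal changes with equal worsening on all three; the condition is met only if none is significant. Correlation is assumed to lie between 0 and 0.8.

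| Worsening on all three | Condition met |
|---|---|
| 0.3 SD | 55–71% |
| 0.5 SD | 20–43% |
| 0.8 SD | 1–10% |

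**Completers (assumed numbers).** At d = 0.5 one scale goes unflagged 59% of the time with 14 patients, 65% with 12 and 71% with 10. The 50% point moves from 0.57 to 0.62 and 0.69 SD.

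**Multiplicity.** At d = 0.5, power per scale is 41% uncorrected and 23% with a Bonferroni correction over three scales (alpha 0.05/3). Leaving p uncorrected preserves power, but 41% is still the most it gives.

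**What 14 patients can exclude.** CI half-width = t(13, 0.975)/√14 = 2.160/3.742 = 0.58 SD, or 0.577 × 20 = 11.5 points on the same assumption.

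**Group means, an invented illustration.** Ten patients worsen by one unit and four improve by one unit. Mean worsening = 6/14 = 0.429; SD = √[(14 − 14 × 0.429²)/13] = 0.938; t = 0.429/(0.938/3.742) = 1.71, below 2.160. The clause is satisfied with 10/14 (71%) worse.

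**The case against.** **The scales are an adjunct.** This is the strongest objection, and it stands. Section 4.3 says the scales are used as well as the questionnaires and EEG, and that they support conclusions. A reader might infer that safety will be declared on non-significance alone; no passage says so. The questionnaires, EEG and neurological exam all work patient by patient.

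**The test is not blind to harm.** This also stands. A reader might infer that the clause would be satisfied under almost any worsening. It would not: at 0.8 SD one scale passes only 21% of the time, and if all three scales worsen by 0.5 SD the condition fails more often than it is met. The single-scale figures describe harm confined to one scale.

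**Uncorrected p-values help.** They do, by avoiding a drop from 41% to 23% power in the example. They do not supply the missing margin.

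**Such detail belongs in an analysis plan.** Margins and tables could be left there. But the article states the inference itself, so the objection does not remove it. If significant was meant clinically, no threshold is given; section 4.4, which ties the safety analysis to p-values, points to the statistical reading.

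**SPMSQ may be scheduled elsewhere.** Section 4.3 gives its timepoints, section 4.2 describes its list as covering motor and non-motor function, and Figure 1 is not shown. It would go too far to say the scale will not be collected. What remains is a secondary inconsistency between the two sections.

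**Conclusion.** The point holds in a limited form. As written, the clause reads non-significance as support for safety without a margin or confidence bound. At n = 14 one scale would more often than not satisfy it up to a true mean worsening of about 0.57 SD of the change. If all three scales worsen equally, that crossover lies between 0.3 and 0.5 SD.

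This rests on normally distributed changes, a two-sided 5% paired t-test from baseline to post-intervention, significance meaning p < 0.05, and 14 completers. The mixed model of section 4.4 was not modelled. Worsening sizes and correlations are assumptions.

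The documents do not support saying that the whole safety assessment is void or that large harm would be missed. The sentence should be corrected before the data are analysed. It leaves the primary outcome and sample size untouched, so it is not a flaw that should stop the trial.

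**What to change.** Replace the sentence in section 4.3 so that non-significance is not read as safety.

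1. Report the mean change on each safety scale with its 95% CI, and state that the half-width is about 0.58 SD at n = 14. Call the result supportive only if the CI excludes a worsening margin that the sponsor fixes for each scale before data are seen.
2. Report the number of patients who worsen by at least that margin from baseline to the post-treatment visit, with an exact 95% CI, and list withdrawals separately. Do not count worsening at any visit. Section 2 gives five post-baseline assessments, and with no true change and a between-visit correlation of 0.5 to 0.8 (assumed), 51% to about 65% of patients would cross 0.5 baseline SD at least once by chance. Even one visit carries noise: Φ(−0.5/√(2(1 − r))) is 31% at r = 0.5 and 21% at r = 0.8. Without a control arm the count is therefore descriptive.
3. Reconcile SPMSQ between sections 4.3 and 4.2: add it to the list, or name a scale already collected, such as SCOPA-COG.

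The cost is wording and one margin per scale, with no extra patients. The downside is that the scale-based statement may be inconclusive. By symmetry with the power figures, if the true mean change is zero the CI would exclude a margin of 0.57 SD only about half the time, and one of 0.81 SD 80% of the time.
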